### Tertiary study outcomes

*Utility of primary sector service* is measured with register-based information on visits to the general practitioner; administrative data on referrals from primary sector, and with a questionnaire on help-seeking behavior adapted from the Attitudes Toward Seeking Professional Psychological Help Measure [37].

*Child physical health, socio-emotional and cognitive development* is measured at nine months by nurse observations of height and weight and ratings online and gross motor skills, problem solving and social skills during home visit. Socio-emotional development is measured with the Ages and Stages Questionnaire [38] at nine months and 18 months. Information about timing of enrolment in and type of non-parental child care and information on school starting age is obtained from registers. These choices have been shown to have long-term effects on child outcomes [39-41].

*Satisfaction with service delivery* is measured with evaluation sheets collected from families receiving the FSP by health nurses at the end of the third program session. A randomization procedure determines which specific three sessions are evaluated within each group. The evaluation sheet covers satisfaction with group sessions, group atmosphere and continuity and use of group network. Information on attendance to sessions, dropout and reasons for dropout is collected by the health nurse program leader at each session.

### 2.E Sample size

Meta-analytic studies on the effects of parenting education with expectant and new parents found on average small effects on measures of parental adjustment (i.e. PSOC) (*d* = .21, [42]). Stronger effects emerged if interventions included more than five sessions, included an antenatal and postnatal component and were led by professionals rather than semiprofessionals. Thus, we expected *d* = .20 to be a conservative estimate of effect on the primary outcome in the present study.

Findings on our secondary outcomes are more varied depending on the measure used. Parental stress as measured by the Parenting Stress Scale showed effect sizes of *d* = .20 [16] and parenting quality as measured with the HOME inventory (nurse observation, [34]) produced average effect sizes of *d* = .35 SD units [16]. Studies relying on parental self-report found somewhat lower effects; [36], for example, found small effects on coparenting quality (*d* = .18 SD units) and somewhat better effects on parenting quality (ranging from *d* = .30 to *d* = .36), and moderate size effects on relationship satisfaction (*d* = .43). In this study we use both the HOME inventory as well as Feinberg’s measures of parenting and coparenting/relationship satisfaction. Thus we expected *d* = .20 to be a conservative estimate of effects on the secondary outcomes in the present study.

Our primary as well as secondary outcomes all produce interval data that are not cardinal in nature. Thus, the value of a given outcome has no meaning in itself. This is clearly in contrast to many outcomes studied in the medical sciences (e.g. number of days admitted to hospital after surgery). One way of anchoring expected effect sizes is to compare to effects of other interventions. In our case, an effect size of .20 in terms of for example parental stress is comparable to average effects of other types of parenting education [16].

Our power analyses use the 2013 version of the Optimal Design software developed by Spybrook and collaborators. Since treatment in this subproject is carried out at the group-level, we conservatively use the two-level cluster-randomized version with family-level outcomes and ignore the presence of covariates. Assuming that 20% of the variation lies between groups and using a power of 0.80 and significance level of 0.05, we are able to detect an effect size of 0.2 with around 230 groups (115 groups in each condition) or a total of 2,070 families.

Assuming that 25% of study participants drop out after randomization and prior to the nine months follow-up, we will need to recruit 280 groups or 2,520 families. According to Statistics Denmark, 4,000 children were born in Aarhus in 2012. Since about 45% of all Danish live births were first born children, and assuming that 80% choose to participate in the research project, detecting such an effect size will roughly require a 1½ year trial; see also 3.A below.

Groups are considered as “did not receive intervention” if 50% of the mothers in a FSP group drop out or if more than two group meetings are cancelled due to group disagreement.

We consider women or men as dropouts from the program if they miss two consecutive meetings without reasonable reason or apologies (such as illness). We categorize women or men as “did not receive intervention” if they do not attend at least two of the postnatal sessions.

We will not base the continuation of recruitment on interim analyses. This is primarily because we expect the intervention to be associated with very low risk for participants. There may be smaller inconveniences, at least for some, associated with the level of time consumption from participating in a program such as FSP. Nevertheless, we will conduct interim analyses and report preliminary results when sample size allows for power of 0.80 to detect an effect size of 0.2 between conditions at the family-level (*N* = 800 families), ignoring group level variation. As explained, however, participation is entirely voluntary and will not affect access to other family services provided by the municipality or the region. Even if the program does not significantly improve participants’ primary outcome in short-term preliminary analyses, this will not lead us to discontinue the program thereby ignoring possible secondary, tertiary and longer term outcomes.

We will perform a dropout analysis that characterizes dropouts in terms of pre-intervention background variables (see list above) if more than 1/3 of study participants (mothers) drop out after initial randomization and prior to the nine months follow-up.

We will discontinue the study if less than 40% of those approached in connection with standard pregnancy scans have accepted to participate in the study after the first six months of recruitment. Similarly, we will discontinue the study if after six months of recruitment more than 2/3 of the women assigned to the FSP condition have dropped out after their initial randomization.

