### Dates defining periods of recruitment and follow-up

Recruitment began on November 24, 2014. Inclusion will continue at least until May 1, 2016. As detailed above, survey data will be obtained at four time points, during pregnancy, when the child is 9 months, 18 months, and 7 years. We will follow the families continuously through register-based data until the child turns 7 years old.

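### The 25% dropout, the target of 280 groups and the 1½-year duration do not agree with one another or with the 230 groups they start from

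*Protocol article*

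**What the plan says.** Section 2.E, Sample size, of the protocol article sets out a chain of figures.

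- **Base size.** The inputs are an effect of 0.2 SD, "using a power of 0.80 and significance level of 0.05", and clustering: "Assuming that 20% of the variation lies between groups". The model is described thus: "we conservatively use the two-level cluster-randomized version with family-level outcomes and ignore the presence of covariates". The result is "around 230 groups (115 groups in each condition) or a total of 2,070 families".
- **Dropout.** A quarter of study participants are assumed lost between randomization and the nine-month follow-up, from which "we will need to recruit 280 groups or 2,520 families".
- **Duration.** From 4,000 births a year in Aarhus, 45% of them first-born, and 80% participation, the section concludes that "detecting such an effect size will roughly require a 1½ year trial".

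The section on dates of recruitment and follow-up gives a start of November 24, 2014 and adds: "Inclusion will continue at least until May 1, 2016". The abstract rounds the target to approximately 2,500 participating women with partners. The Randomization section states that allocation is by family.

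**The concern.** Each step is presented as following from the one before: a base size, a target inflated for dropout, and the time needed to reach it. A reader who redoes the two later steps with the stated inputs gets different answers. The target of 280 groups is not what a 25% loss requires under either reading of that loss, and the stated duration does not produce the stated target at the stated accrual rate.

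The recruitment target is the protocol's main quantitative commitment. The plan also says that continuation of recruitment will not depend on interim analyses, so the target and the calendar are its main guides to when enough families are in. If the two disagree, someone must choose between them later, and the document does not say what power each choice gives.

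**Working it through.** **Inputs** (2.E Sample size unless noted): d = 0.20; ICC ρ = 0.20; α = 0.05; power 0.80; nine families per group (2,070/230 = 9 and 2,520/280 = 9); two equal arms; 25% loss; 4,000 births, 45% first-born, 80% participation. Start November 24, 2014 and minimum end May 1, 2016 come from the section on dates. Sidedness is not stated. I assume two-sided, which reproduces 230; one-sided would give 180.

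**Step 1. Reproduce the base size.** For J groups of n families, λ = d / √[4(ρ + (1 − ρ)/n)/J], with power from the non-central t on J − 2 degrees of freedom. At J = 230, n = 9: λ = 0.2 / √[4(0.2 + 0.8/9)/230] = 2.82 and power is 0.802. The smallest J reaching 0.80 is 229. The stated 230 groups / 2,070 families is correct.

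**Step 2. Apply the 25% loss.**

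- Analysed groups stay at nine, so the group count is inflated: 2,070/0.75 = 2,760 families; 230/0.75 = 306.7, so 307 groups (308 for equal arms).
- Individual loss thins groups to 9 × 0.75 = 6.75 families: the same formula needs 252 groups, that is 252 × 9 = 2,268 families recruited.
- Multiplying by 1.25 instead of dividing by 0.75, a common slip, gives 288 groups / 2,588 families. This is close to 280 / 2,520 but not equal to it.
- Working back from the target: 1 − 230/280 = 17.9% loss. Also 2,520 × 0.75 = 1,890 families, 180 below 2,070.

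**Step 3. Duration.** 4,000 × 0.45 × 0.80 = 1,440 families a year.

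- 2,520/1,440 = 1.75 years, or 21 months, to about late August 2016.
- 1.5 × 1,440 = 2,160 families (240 groups), 360 below target.
- Reaching 2,520 in 1.5 years would need 2,520/(4,000 × 0.45 × 1.5) = 93% participation instead of 80%.
- November 24, 2014 to May 1, 2016 is 524 days: 524/365.25 × 1,440 = 2,066 families.

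**Step 4. Power under the plan's model with 25% loss.**

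| Families recruited | Groups | Individual loss (n = 6.75) | Whole groups lost (n = 9) |
|---|---|---|---|
| 2,520 (stated target) | 280 | 0.84 | 0.77 (210 remain) |
| 2,160 (1½ years) | 240 | 0.78 | 0.70 (180 remain) |
| 2,066 (to May 1, 2016) | about 230 | 0.76 | 0.68 (about 172 remain) |

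Letting group size vary binomially instead of fixing it at 6.75 changes the first column little (0.837 at 280 groups, 0.777 at 240).

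**Step 5. Clustering in the FSP arm only.** Families are randomized individually and only the FSP arm meets in groups. With m analysed families per arm, the variance of the difference is [1 + (n − 1)ρ]/m + 1/m. For 2,160 recruited with individual loss, m = 810 and n = 6.75: (2.15 + 1)/810 = 0.00389, 0.2/√0.00389 = 3.21, power about 0.89 (normal approximation). The same calculation gives about 0.93 at 2,520 and about 0.88 at 2,070 recruited.

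**The case against.** The strongest reply is that little depends on this, and much of it stands.

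A reader might infer from the faulty inflation that the trial misses its 80% power. The document does not support that. Loss is stated for study participants, which most naturally means individual loss. With ρ = 0.20, losing families within groups costs far less than losing groups, so 280 groups still give about 0.84 and 252 would do. The 0.77 figure requires whole groups to leave the analysis. The rule labelling a depleted FSP group as not having received the intervention does not do that, because the analysis is by intention to treat.

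A reader might also infer that recruitment closes on May 1, 2016 with about 2,066 families, in effect the size with no dropout allowance. The text gives that date as a minimum, and the target remains 2,520. The near-match with 2,070 therefore does not show that the allowance has been lost, and the 0.76 and 0.68 figures apply only if inclusion actually stops there.

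The cluster-randomized model is also openly conservative: it clusters both arms and ignores covariates, although ANCOVA is planned. Under clustering in the FSP arm only, every individual-loss scenario above exceeds 0.80. The fallback to group-level randomization in a district would cluster both arms there, but it is contingent.

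Finally, the duration is worded as rough. That softens a three-month gap but does not remove it: 21 months is one sixth longer than 18, and 2,160 families is 360 short of the target. None of these replies makes 280 groups follow from 230 with 25% loss.

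**Conclusion.** The inconsistency is real and moderate. The base size of 230 groups is right. The dropout rate, the inflated target and the duration cannot all hold together: 25% loss leads to 307 groups (308 for equal arms) or to 252, according to how the loss falls, and 280 is neither; 2,520 families need about 21 months, and 1½ years brings 2,160.

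The inflation error alone does not show that 80% power is missed. A shortfall under the plan's own model arises at 280 groups only if whole groups are lost (about 0.77), or if inclusion stops near 1½ years (about 0.78 with individual loss, 0.70 with whole groups lost). The protocol commits to neither.

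This rests on a two-sided test, groups of nine at recruitment, ICC 0.20, constant accrual at the stated rate, and equal loss in both arms. The accrual rate shows no separate deduction for the exclusion criteria. The document gives no figure for that, so it is not used here; any such deduction would lengthen recruitment.

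**What to change.** Make the three figures consistent in one of two ways.

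- **Keep 2,520 families.** State the dropout model behind the figure and its power under the cluster model: about 0.84 with individual loss, about 0.77 if whole groups are lost. Restate the duration as about 21 months at 1,440 families a year, with inclusion expected to reach the target around late August 2016.
- **Keep 1½ years.** State that about 2,160 families are expected, and the power they give under the cluster model: about 0.78 with individual loss, about 0.70 if whole groups are lost.

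In either case, add a sentence noting that the cluster-randomized model is conservative because families are randomized individually, and report power with clustering in the FSP arm only as a separate figure.

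The cost is a few corrected sentences in the sample size section and, under the first option, a later expected end of inclusion. Recruitment need not rise, and no outcome, test or design feature changes.

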### Blinding

The research team and families remain blind to study condition during recruitment, consent and baseline questionnaire, though blinding after this point in time is not possible.

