### Statistical methods

Reporting of results will follow the guideline of the CONSORT- statement. Statistical analysis will be intention to treat. The level of significance will be 0.05. The primary endpoint is PSOC at the nine month follow-up. The intention-to-treat analysis will compare FSP with TAU using both simple two-sample t-tests, non-parametric rank based tests (Wilcoxon), and linear regressions (ANCOVA) that control for pre-randomization variables (parents’ age, marital status, educational background, employment status, previous psychiatric/therapeutic treatment, smoking, place of birth, own number of siblings, receipt of welfare, financial strain, and social desirability). This latter analysis will cluster errors at the FSP group level. Except for the divorce rate at the seven year follow-up, which is binary in nature, all statistical analyses of effects on secondary outcomes will follow our strategy for the primary outcome. For divorce rate, we will use simple two-sample t-tests as well as a logistic regression that control for pre-randomization variables. Similar principles will be applied to the analysis of tertiary outcomes.

In addition to intention-to-treat analysis, we will also perform contamination adjusted intention-to-treat analysis, which complements the intention-to-treat approach by producing a better estimate of the benefits and harms of receiving a treatment. This method uses the statistical technique of instrumental variable analysis to address contamination [41-46].

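### The interim report is triggered at 800 families as having 0.80 power, but under the plan's own 20% between-group variance the power is about 0.41 to 0.56

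*Protocol article*

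**What the plan says.** Two calculations stand in the protocol article, section 2.E Sample size.

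- **Main calculation.** Because the programme is delivered in groups, the authors write that "we conservatively use the two-level cluster-randomized version with family-level outcomes and ignore the presence of covariates". The inputs are given as "Assuming that 20% of the variation lies between groups and using a power of 0.80 and significance level of 0.05". The result is about 230 groups, 115 per condition, or 2,070 families, for an effect of 0.2.
- **Interim look.** Further on in the section, "we will conduct interim analyses and report preliminary results when sample size allows for power of 0.80 to detect an effect size of 0.2". The size is given as "800 families), ignoring group level variation".

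The section also says that the interim will not decide whether recruitment continues. A non-significant preliminary result on the primary outcome would not end the programme.

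Statistical methods gives one general level: "The level of significance will be 0.05". It lists three comparisons of FSP with TAU: a t-test, a Wilcoxon test and an ANCOVA. Only the ANCOVA is said to cluster errors by FSP group. The adjustment for multiplicity described there is for several outcomes, not for repeated looks.

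**The concern.** The two calculations use the same effect size and the same power for the same comparison, but opposite assumptions about clustering. The smaller number is reached only by setting to zero the variance component that drives the larger one, and no reason is given why groups should matter at the end of the trial but not at the interim.

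What is at stake is how the preliminary report will be read. A null result from an analysis described as having 80% power looks like evidence against an effect of 0.2. If the real power is near one half, it is little evidence either way. In the other direction, a test that ignores the grouping has a standard error that is too small, so a positive preliminary result could come from clustering alone.

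**Working it through.** **Inputs from the protocol article.** Effect d = 0.2, power 0.80, significance level 0.05, 20% of variance between groups (ICC 0.20), and 2,070 families in 230 groups (nine per group), all from 2.E Sample size. Allocation is 1:1 (Randomization), so 800 families means 400 per arm. FSP groups are formed only from families assigned to FSP (Randomization).

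**Assumptions of this check.** The test is two-sided (not stated, but it reproduces both of the plan's figures). The outcome has total variance 1 in each arm. The 800 are families with nine-month data.

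**1. Reproduce the 800.** For independent families, n per arm = 2 × (1.96 + 0.842)² / 0.2² = 392.4, so 393 per arm or 786 in total. With 400 per arm the power is 0.807. The 800 is right on its stated basis.

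**2. Reproduce the 2,070.** Design effect = 1 + (9 − 1) × 0.20 = 2.6. With 1,035 per arm, SE = √(2 × 2.6 / 1,035) = 0.0709 and d/SE = 2.82. Power is 0.802 (t, 228 df) or 0.806 (normal). This also reproduces.

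**3. Put the plan's ICC into the interim.**

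| Model at 800 families | Variance of the difference | SE | d/SE | Power |
|---|---|---|---|---|
| Both arms clustered (the plan's model) | 2 × 2.6 / 400 = 0.0130 | 0.114 | 1.75 | 0.41 (t) to 0.42 (normal) |
| FSP arm only | (2.6 + 1) / 400 = 0.0090 | 0.0949 | 2.11 | 0.55 (t, Satterthwaite df of about 82) to 0.56 (normal) |

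With the smaller df from the number of FSP groups alone (about 43), the second row falls to 0.54. Power of 0.80 would need about 786 × 2.6 = 2,044 families in the first model, and about 2 × (1.96 + 0.842)² × 3.6 / 0.04, or 1,413, in the second.

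**4. Sensitivity.**

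- If 800 means families recruited and 25% drop out, 600 are analysed at 6.75 per group on average, and power is about 0.39 (both arms) to 0.50 (FSP only).
- With groups of seven or eight, it is about 0.44 to 0.61 across the two models.
- If within-group variance is 1 in both arms and FSP adds 0.25 between groups, power is about 0.49.
- At an illustrative ICC of 0.05 (not in the plan), the design effect is 1.4 and power is 0.67 to 0.73.

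None reaches 0.80.

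**5. Type I error of an unclustered interim test.** The naive variance is 2/400. The true variance is larger by a factor of 2.6 (both arms) or 3.6 / 2 = 1.8 (FSP only). The effective critical value is 1.96 / √2.6 = 1.216 or 1.96 / √1.8 = 1.461. Two-sided type I error is then 22% or 14%. This concerns the t-test, and approximately the Wilcoxon test, but not the clustered ANCOVA.

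**6. Conditional: two looks each at 0.05.** Expected nine-month data are 2,520 × 0.75 = 1,890 families, so the information fraction at 800 is 0.42 and the correlation of the two test statistics is √0.423 = 0.65. Two valid tests at 0.05 give an 8.6% chance of at least one false positive (8.7% with 2,070 as the denominator). This matters only if the first look is read as a confirmatory test.

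**The case against.** The strongest reply is that nothing is hidden or miscalculated. The caveat stands in the same sentence as the 0.80, the arithmetic is right on that basis, the look is called preliminary, and no decision on recruitment hangs on it. The main calculation is also described as conservative, so the true ICC may be below 0.20. All of this stands, and it lowers the severity. It does not remove the inconsistency: the document gives no ground for dropping the clustering at the interim, and stating an assumption does not make it agree with the other one.

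Some stronger readings are tempting but not supported.

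- **That the interim test will ignore clustering.** A reader might infer this, but the phrase about group variation qualifies the power condition that fixes the size. It does not describe the analysis. The 14% to 22% therefore apply only to the t-test and Wilcoxon test, which the plan leaves unclustered at the final analysis as well.
- **That the interim is to be tested at an unadjusted 0.05.** The protocol article gives one general level and is silent on an interim level. The statistical analysis plan is not shown and could set one.
- **That the trial's overall type I error is 8.6% or more.** No rule for stopping early or claiming success is attached to the look, so this is conditional on a confirmatory reading. Such a reading is possible, since the section does contemplate a significance result on the primary outcome at that stage.
- **That early release will bias later PSOC answers.** Families know their condition ("though blinding after this point in time is not possible") and PSOC is self-reported, so a route exists. The documents do not say that participants or group leaders will see the results, and no size can be given. On the plan's figures, 4,000 × 0.45 × 0.80 / 12 = 120 families join per month, so 800 enrol in about seven months. If they enrol at 12 to 19 weeks and deliver at term, their nine-month data arrive after the planned 1½ years of recruitment. Only later nine-month surveys could be touched.

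**Conclusion.** The point holds for power. On the plan's own inputs, the interim at 800 analysed families has power of about 0.41 to 0.42 with both arms clustered, or about 0.55 to 0.56 with clustering in the FSP arm only, and not 0.80. A true effect of 0.2 would be missed roughly 44% to 59% of the time. This rests on ICC 0.20, nine families per group, 1:1 allocation and a two-sided 0.05. The upper figures also depend on equal total variance in the two arms. A lower ICC would narrow the gap, but the plan gives no other value.

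The type I error of 14% to 22% is a secondary point confined to the unclustered tests. The inflation over two looks arises only if the preliminary result is treated as confirmatory. This should be fixed, but it is not a critical flaw.

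**What to change.** In 2.E Sample size:

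- Delete the 0.80 claim for the interim, or restate it as about 0.41 to 0.56 under the ICC of the main calculation, naming the two clustering models.
- State that any reported interim comparison of FSP with TAU on PSOC uses the model with FSP-group clustering.
- State that the interim is preliminary and non-confirmatory, and that the final analysis is the only test of the primary outcome.
- Preferably, withhold the interim PSOC comparison until the nine-month surveys are complete.

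If the authors do want the early look to count as a test, they need a group-sequential level for it and a matching level for the final analysis.

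The cost is a few sentences of protocol wording, and preliminary reporting that is later or more cautious. Recruitment and the final sample size do not change.

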### Specific objectives and hypotheses

The aims of this study is to determine whether a group-based parent support program can lead to:Early improved parental sense of competence (primary outcome)Continued improvement in parental sense of competence (secondary outcomes)Reduced parental stress (secondary outcomes)Improved quality in early family relationships, that is improved quality of parenting, coparenting and couple relationship quality (secondary outcomes)Improved efficiency in service delivery, that is increasing surveillance of families at risk, and enhancing families’ utility of community resources, social network and family services (tertiary outcomes)Improved child outcomes including better physical health and improved socio-emotional and cognitive development (tertiary outcomes)Heterogeneity of effects across family type with disadvantaged families and families met with a more mature program implementation gaining more from participation (tertiary outcomes).

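### Preliminary arm comparisons on the self-reported primary outcome are to be reported at 800 families, while many nine-month outcomes are still uncollected and without any late-period families

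*Protocol article*

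**What the plan says.** Under *2.E Sample size*, the protocol article first says that continuation of recruitment will not rest on interim analyses. It then commits to them all the same: "we will conduct interim analyses and report preliminary results when sample size allows". The trigger is 80% power at a standardised difference of 0.2, evaluated "between conditions at the family-level (*N* = 800 families), ignoring group level variation". The same paragraph foresees the case that the programme "does not significantly improve participants’ primary outcome in short-term preliminary analyses" and says that this would not lead to discontinuation. The interim therefore includes the primary outcome, and its results are to be reported.

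Other sections bear on this:

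- *Primary study outcome* and *Statistical methods*: the primary endpoint is PSOC at nine months, a parent self-report.
- *Blinding*: families and research team are blind up to the baseline questionnaire, "though blinding after this point in time is not possible".
- *Secondary* and *Tertiary study outcomes*: nurses rate the child at nine months, and the HOME inventory is intended as nurse data.
- *Specific objectives and hypotheses*: the plan expects "families met with a more mature program implementation gaining more from participation". *Statistical methods* defines early (first six months), mid-period (months 7 to 12) and late (after month 12) recruits to test this.
- *Dates defining periods of recruitment and follow-up*: "Inclusion will continue at least until May 1, 2016".

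The article states no limit on who sees the preliminary results and no delay until nine-month collection is complete.

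**The concern.** Two separate things follow from releasing an arm comparison at 800 families.

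The first is reporting. Parents who know their arm rate their own competence. If they learn before their nine-month survey whether the programme appears to work, their answers may shift. The same applies to nurses who rate children or homes, and to attendance in groups still running. Attendance matters for the analysis: attending fewer than two postnatal sessions classes a parent as not having received the intervention, which bears on the contamination-adjusted analysis. The direction of any shift cannot be predicted.

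The second is what the preliminary figure estimates. The 800 families are those enrolled first. If benefit grows as the programme matures, as the plan hypothesises, an estimate without late recruits sits below the effect in the whole trial.

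Against these risks, the plan names no trial decision that the early release would serve. The power and significance level of the interim are a different matter and are not at issue here.

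**Working it through.** **The plan's own figure.** For d = 0.2, two-sided alpha 0.05 (sidedness assumed) and power 0.80, ignoring clustering: n per arm = 2 × (1.960 + 0.842)² / 0.2² ≈ 393, so 786 in total. With 400 per arm the power is 0.807. The stated 800 reproduces.

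**Inputs from the article.** 4,000 births a year, 45% first-born, 80% participation, 25% dropout before nine months, and a target of 2,520 families (*2.E Sample size*). Start on 24 November 2014 and inclusion at least to 1 May 2016 (*Dates*). Recruitment at week 12 or 19 (*Setting*). **Assumed:** term at 40 weeks, even accrual, and 800 meaning families with a nine-month outcome.

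**When 800 is reached.**
- Accrual: 4,000 × 0.45 × 0.80 = 1,440 a year, or 120 a month.
- Families to randomize: 800 / 0.75 = 1,067.
- Time: 1,067 / 1,440 = 0.741 years, about 21 August 2015.
- Add 21 weeks (entry at week 19) or 28 weeks (entry at week 12) to birth, then 39 weeks: 14 October to 2 December 2016.

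**When collection ends.**
- Close on 1 May 2016: 524 days × 1,440 / 365.25 = 2,066 families. Last nine-month outcomes fall from 25 June to 13 August 2017.
- Close at 2,520 families: 2,520 / 120 = 21 months, about August 2016. Last nine-month outcomes fall about October to December 2017.

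**Share outstanding at release.** Dropout cancels from the shares.

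| Release | Close 1 May 2016 | 2,520 families |
|---|---|---|
| Day the 800th outcome arrives | 1 − 800/1,549 = 48% | 1 − 800/1,890 = 58% |
| 3 months later | (2,066 − 1,427)/2,066 = 31% | (2,520 − 1,427)/2,520 = 43% |
| 6 months later | (2,066 − 1,787)/2,066 = 14% | (2,520 − 1,787)/2,520 = 29% |

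Here 1,549 = 2,066 × 0.75, 1,890 = 2,520 × 0.75, 1,427 = 1,067 + 360 and 1,787 = 1,067 + 720. On the first row, about 749 and 1,090 families would still have an outcome to report. If 800 instead meant enrolled families (600 outcomes), the first row would read 61% and 68%.

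**Programme delivery.** With a 1 May 2016 close, the last recruits reach term on 25 September (entry at week 19) or 13 November 2016 (week 12), about 19 days before the matching date for the 800th outcome. Their postnatal sessions start at one month, so these lie ahead if release is prompt.

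**Who is in the interim.** The first six months give 720 families.
- Interim: 720/1,067 = 67% early, 33% mid-period, 0% late.
- Full window to 1 May 2016: 720/2,066 = 35% early, 35% mid-period, 30% late.

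**What that could do to the estimate.** The article gives no effects by period, so the following are assumptions. With 0.10/0.20/0.30 SD for early/mid/late, the interim expects 0.13 against 0.195 for the full window. With 0.15/0.20/0.25 SD it expects 0.166 against 0.198. With equal effects there is no gap.

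**The case against.** The best defence is that the release is harmless by design. Parents already know their arm, results are labelled preliminary, the interim is non-binding, and the early/mid/late comparison is prespecified. The article does not say who receives the preliminary results, and a condensed article may leave access rules to the full protocol. The wording about sample size fixes an earliest moment, not a release date.

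Several of these points stand, and they rule out stronger readings that a reader might infer:

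- *Results will go to families or nurses.* No section says so. What is stated is that results will be reported; exposure of remaining respondents is plausible in a single municipality, not documented.
- *Half of the outcomes are necessarily outstanding.* The 48% and 58% apply on the day the 800th outcome arrives; any lag for analysis lowers them.
- *Only early-phase families are included.* By the plan's own definition, about a third are mid-period. What holds is that none are late.
- *The preliminary estimate will be low by a known amount.* Greater gain with maturity is a tertiary hypothesis, and the gaps above rest on assumed effects. They are 0.03 to 0.06 SD, below one standard error of the 800-family comparison (√(2/400) = 0.07 SD even without clustering).
- *The final estimate is understated.* The make-up of the interim sample has no bearing on the final analysis.

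What does not stand is that being non-binding settles the matter. That answers the worry about stopping, not disclosure. Knowing one's arm is also different from being told that the arm appears to work or not.

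**Conclusion.** The point holds in limited form. The article commits to reporting an arm comparison on a self-reported, unblinded primary outcome before collection of that outcome is complete, with no stated embargo and no trial decision that needs it.

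The outstanding share is about 48% to 58% at the trigger, and about 14% to 43% if release follows three to six months later. This rests on the plan's accrual and dropout figures, even accrual and a 40-week term. The size and direction of any effect on the remaining reports, nurse ratings or attendance are unknown.

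The second part is narrower. The preliminary figure would describe first-enrolled families and, if the maturity hypothesis is true, would lie below the full-trial effect by an unknown amount.

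This is a cheap improvement to the plan rather than a flaw that undermines the trial.

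**What to change.** Amend the interim paragraph in *2.E Sample size* to state that:

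- no arm-comparison result leaves the analysis group until nine-month data collection, both survey and nurse visit, is closed;
- any look at 800 families stays confidential until then;
- if that look is later shown, it is described as the first-enrolled families with no late-period recruits, and not as the early subgroup defined in *Statistical methods*, which it does not match.

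The cost is a few sentences and a later preliminary report: about 8 months later with a 1 May 2016 close ((2,066 − 1,067)/120 = 8.3), or about 12 months with 2,520 families ((2,520 − 1,067)/120 = 12.1).

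This protects the nine-month primary endpoint. It does not protect all 18-month and seven-year self-reports, many of which would still follow release of the nine-month results.
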